## Data collection

Designated interviews will conducted the patient interviews and these researchers will not be part of the treatment or chief investigator research team.

All interviews will be;

- Conducted within 4 weeks of treatment completion.
- Conducted over the phone
- Audio-recorded and transcribed verbatim, and field notes will be taken during and after each interview
- Open-ended and carried out as a conversation to understand the participant's treatment experience, with respect to tolerability and satisfaction, within the trial
  - An interview script with a set of standardised questions will be provided to the interviewer for consistency between interviews (see **APPENDIX 5: Qualitative Review of the patient experience of non-operative treatment in early-stage hepatocellular carcinoma: Example interview script**).

It is anticipated that each interview will take approximately 20 minutes to complete.

## Data Storage

Recordings of interviews will be allocated a unique study ID prior to being sent for transcription.

All data and digital recordings and will be stored securely, in a password protected computer and only the study investigators will have access to the data.

Participants will be given the option of requesting the transcript to check their answers.

## Analysis

A grounded theory approach will be used to analyse the data. This approach for content analysis is interpretive in nature and used to describe or illuminate a phenomenon through identification of manifest (the obvious) and latent (underlying meaning) content in a text. This will involve:

- - 1. reading of the text several times to become familiar with it and reflect upon the content,
    2. identification in the text of meaning units that describe the phenomenon,
    3. meaning units condensed and essential content is abstracted and labelled with a code, and
    4. codes compared based on similarities and differences sorted into themes. Coding and sorting of themes will be assisted using the analysis tool NVivo.

# WITHDRAWAL FROM TREATMENT OR WITHDRAWAL FROM STUDY

At any time, participants are free to discontinue study treatment or withdraw from the study without prejudice to further treatment.

- Where applicable, the participant will be asked about the reason(s) for discontinuing study treatment or withdrawing from the study.
- Where possible, the investigator will perform the best possible observation(s), test(s) and evaluation(s) as well as provide appropriate medication and all give possible measures for the safety of the participant. Ongoing adverse events will be assessed by an investigator and followed, either during scheduled study follow-up or, in the case of withdrawal of consent, outside of the clinical study.

The trial coordinating centre is to be notified of the discontinuation of study treatment and/or withdrawal from the study as soon as possible.

The status of ongoing, withdrawn (from the study) and “lost to follow up” participants at the time of an overall survival analysis should be obtained by the site personnel by checking the participant notes, hospital records, contacting the participant or their general practitioner and checking publicly available death registries.

## Discontinuation of a participant from treatment

Participants may be discontinued from treatment in the following situations:

- Participant decision
- Adverse event
- Severe non-compliance with the study protocol as judged by the investigator and/or TMC.
- Participant incorrectly initiated on study treatment.
- If the treating investigator believes the participant is no longer receiving clinical benefit from treatment and/or requires additional anti-cancer treatment

Study procedures related to SAEs and anti-cancer treatment must be captured until permanent withdrawal from the study.

Participants who stop study involvement prior to the time recommended in the protocol will be requested to continue follow-up visits according to the protocol.

If a participant wishes to stop the study visits, they will continue to receive ongoing care as per their treating team. Study investigators may request an update regarding their ongoing health status via their medical records unless the subject has withdrawn consent.

## Withdrawal from Study

The term withdrawal from the study refers to both discontinuation from study treatment AND study assessments.

Reasons for withdrawal from the study:

- Death
- Withdrawal of consent

If a participant wishes to withdraw their consent to both treatment and study assessments, they should be asked if they are willing to continue with survival follow up (which can be conducted by telephone).

Regardless of the reason for withdrawal, all data available for the participant at the time of discontinuation of follow up must be recorded. All reasons for discontinuation of treatment must be documented.

If a participant wishes to withdraw their consent to further participation in the study entirely, including survival follow up, this should be clearly documented in the participant notes.

## Participant transfers

Every effort should be made for a trial participant moving from the area to continue their treatment and/or follow-up at another participating Trial Site and for this Trial Site to take over responsibility for the participant.

Until the new Trial Site formally agrees (in writing) to take over responsibility and provides evidence of ethics approval, the participant remains the responsibility of the original Trial Site. Source documentation will remain at the original Trial Site up to the date of transfer.

# TERMINATION OF THE STUDY

The study may be stopped if in the judgement of the Sponsor and TMC, if trial participants are placed at undue risk because of clinically significant findings that:

- Meet individual stopping criteria or otherwise considered significant.
- Are assessed as causally related to study treatments.
- Are not considered to be consistent with the continuation of the study.

Should the study be terminated, the Sponsor will ensure that adequate consideration is given to the protection of the participants’ interests.

# SAFETY REPORTING AND MEDICAL MANAGEMENT

## Definitions

**Adverse Event (AE):** An AE is any untoward medical occurrence (toxicity, sign, symptom, abnormal result on an investigation or disease temporally associated with the use of a medicinal product) in a patient administered a study treatment; the event does not necessarily have a causal relationship with the treatment.

The term AE is used to include both serious and non-serious AEs.

**Serious Adverse Event (SAE):** An SAE is any untoward medical occurrence that occurs between consent and 28 days after cessation of treatment interventions, that fulfils one or more of the following criteria:

- Results in death
- Is immediately life-threatening (an event in which the participant was immediately at risk of death *at the time of event*)
- Requires in-patient hospitalisation or prolongation of existing hospitalisation
- Results in persistent or significant disability/incapacity
- Is a congenital anomaly/birth defect
- Important medical event (events may be considered a serious adverse experience if they require medical or surgical intervention to prevent one of the listed definitions, e.g. an ‘allergic bronchospasm’ which required intensive treatment in an emergency room or at home)

An event will not be considered to be a SAE if;

- Hospitalisation is due to administration of trial procedures
- Hospitalisation is due to placement of a permanent intravenous catheter
- Hospice placement for terminal care is required
- Hospitalisation is due to pre-trial scheduled elective surgery
  - Out-patient hospitalisation for procedures such as:
  - Elective day surgery
- Convenience purposes (e.g. transportation difficulties)
- Death is due to cancer (this is considered ‘expected’ and is therefore not a SAE)
- Any new cancer is diagnosed that does not meet the SAE criteria (this is to be reported on relevant CRF).

## Adverse event (AE) reporting

### Adverse Events (AE)

Adverse events are to be reported between from consent and 28 days after all the last study treatment [list study treatments] is discontinued and must be graded according to The National Cancer Institute (NCI) Common Terminology Criteria for Adverse Events (CTCAE) version 5.0 by a delegated staff member. For each AE, the highest grade observed since the last visit should be reported on the relevant CRF.

All non-serious adverse events (including anticipated and unanticipated device related adverse events) shall be recorded in the trial database via adverse event CRFs. Internal statistical analysis of these data shall be performed at the times specified in the protocol and investigators and responsible ethical committees will be advised of any safety issues which emerge during this process.

Any AEs that are unresolved at the participant’s last visit in the study are followed up by the investigator for as long as medically indicated, but without further recording in the CRF. The TMC retains the right to request additional information for any participant with ongoing AE(s) at the end of the study, if judged necessary.

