## Rationale for choice of primary endpoint

The aim of any local therapy is to maximise local control whilst minimising toxicity and any impact on functional reserve. This study is powered to detect a clinically relevant improvement in the primary endpoint of 2 year freedom from local progression (FFLP) with progression free survival (PFS), overall survival (OS), toxicity and patient reported outcomes representing important secondary endpoints. Whilst overall survival is considered the most robust efficacy endpoint for an intervention it can be confounded by the multitude of effective downstream therapies available and their subsequent effects on progression of tumour and underlying liver dysfunction.(43, 44) This is particularly the case when evaluating therapies in early stage HCC. For HCC multiple sequential local therapies are often employed whilst the disease remains in an early stage and hence, the trial investigators consider it impractical to limit post-progression therapy, including the option of cross-over therapy in the event of local or other intra-hepatic progression. Demonstration of a significant improvement in local control without increased toxicity within the context of a randomised trial would provide evidence to support the inclusion of SABR as an initial treatment option for single HCC (BCLC-O/A).

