“Atypical” intrahepatic lesions are defined in mRECIST as non-enhancing or rim enhancing lesions. These features can be seen in well differentiated, steatotic or poorly differentiated tumours and have often undergone biopsy confirmation. For these lesions RECIST v1.1 criteria, i.e. overall tumour diameter measurements, should apply. A new atypical intrahepatic lesion is regarded as equivocal until interval growth ≥10mm is demonstrated on subsequent scans.

Whilst mRECIST has advantages for response assessment in the setting of thermal ablation, TACE and some systemic therapies, the distinct mechanism of action of radiation-based therapies introduces further challenges. For radiation-based therapies such as radio-embolisation and SABR, both persistent arterial phase hyperenhancement within the target lesion and geographic arterial phase hyperenhancement without washout in the adjacent parenchyma are common in the first 3-12 months following treatment.(45) In contrast to thermal ablation or TACE, residual enhancement in this period is not predictive of subsequent local progression. (46)

The distinct natural progression of target lesion and adjacent parenchymal changes following SABR has been illustrated by Mendiratta-Lala and colleagues.(46) In the first 3 to 12 months following SABR, the arterial phase hyperenhancement gradually converts to portal venous and delayed phase hyperenhancement, as radiation induced veno-occlusion and fibrosis develops, with overlying capsular retraction. Lack of washout or other features such as diffusion restriction can help differentiate expected post-radiation perfusional changes from infiltrative tumour. Radiation-induced biliary strictures, and their associated distal segmental changes, can develop after SABR for more central tumours. Despite mRECIST response having a lower predictive ability in the early months following SABR, with the majority demonstrating stable disease, subsequent new nodular or increasing volume and intensity of arterial phase hyperenhancement with washout are indicators of progressive disease.

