## Objectives

**Table 2: Objectives and Endpoints**

|  | **OBJECTIVE** | **ENDPOINT** |
| --- | --- | --- |
| **PRIMARY** | Evaluate the efficacy of SABR compared to SOC first line therapies in terms of local lesion control | 2-year FFLP according to mRECIST ( or RECIST v1.1 when mRECIST can’t be used) |
| **SECONDARY** | Evaluate progression-free survival | 2-year PFS |
|  | Evaluate overall survival | 2-year OS |
|  | Evaluate safety and adverse events | Cumulative incidence of adverse events (CTCAE v5) |
|  | Compare patient reported outcomes between SABR and SOC therapies | EORTC QLQ-C30 and QLQ-HCC18 - mean scores over time. Time to ≥10 point decrease in the combined GHS/QoL score. |
|  | Cost-effectiveness analysis | Incremental cost per outcome (additional patient with FFLP at 2 years; and quality adjusted life years) for SABR compared with SoC. |
|  | Qualitative review of patient experience | Patient treatment experience assessed by qualitative methods |
| **EXPLORATORY** | To identify biomarkers associated with treatment outcome. | Changes in serum AFP, haematological and liver function parameters post-treatment. |

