### Post Randomisation

Visits will occur from 3 months post-randomisation in 3 monthly intervals (+/- 2 week) to 2 years and then 6 monthly (+/- 2week) until completion of the trial and are to include;

- Blood tests:
  - Clinical chemistry: AST, ALT, ALP, GGT, total bilirubin, albumin, creatinine, sodium
  - Haematology: Hgb, WCC, Neuts, Lymph, Plts
  - Coagulation: PT, APTT, INR
  - AFP
- Clinical assessment including:
  - ECOG Performance status
  - Presence of ascites or encephalopathy and Child Pugh score
  - Weight and body mass index
  - Adverse event reporting (CTCAE v5.0)
    - *Assessment of toxicity is continuous and will include any event occurring between assessments*.
  - Concomitant medications
  - Recording of any additional investigations or events performed or hospitalisations (required for Health economics analysis)
- Disease assessment:
  - Abdominal Imaging: Multiphase contrast-enhanced CT or MRI of the liver
    - In the individual patient it is recommended that the same imaging modality is used throughout the study for more reliable response assessment.
    - See **APPENDIX 3: Imaging Guidelines** for recommended sequences.
  - See **Section 8 DISEASE PROGRESSION** for further details on assessment for disease progression.

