### Serious Adverse Events (SAE)

SAEs are to be reported to the TCC by the trial site within 24 hours of being notified, from consent and within 28 days from the completion of treatment [SABR, RFA, MWA, TARE, TACE] is completed/discontinued.

The investigator at the trial site is responsible for;

- grading the event according to the [NCI CTCAE vs 5](chrome-extension://efaidnbmnnnibpcajpcglclefindmkaj/https:/ctep.cancer.gov/protocoldevelopment/electronic_applications/docs/ctcae_v5_quick_reference_5x7.pdf)
- identifying the seriousness of the adverse event
- identifying the causal relationship to the treatment (see **Table 8: Definitions of causality**)
  - attribution to the SAE must be recorded in the patients’ medical records and reported on the SAE form
- identifying the causal relationship in relation to other medication
- determining the expectedness according to the Investigators Brochure (medicinal products)
- reporting to their local approving authorities as per local guidelines
- to follow-up the event until resolution or death

The initial SAE report should always include at least the following information; participant number, suspected medicinal produce if applicable, identifiable reporting source, description of medical event, seriousness criteria and causality assessment by the investigator. Remaining information must be forwarded to the TCC as soon as possible, but no later than 7 calendar days from the initial report.

The investigator is also responsible for notifying responsible HRECs, Research Governance Officers or other appropriate regulatory authorities of the SAE according to local ethical and regulatory guidelines. They are also to follow up the event (with regular reporting) until resolved.

The trial coordinating centre (TCC) shall;

- Implement and maintain a suitable recording system to record information from all SAEs received from Trial Sites.
- On receipt of an SAE, arrange for the trial chairpersons and/ or a clinical reviewer to review the event and confirm causal relationship and expectedness
- Report all SAEs to TROG Cancer Research
- Notify the sponsor (TROG Cancer Research) and all other participating investigators of any serious unanticipated related adverse events and any action taken
- Notifying the regulatory authorities of each country of any significant issue that has arisen from analysis of overseas reports or action that has been taken by another country’s regulatory authority in reporting timelines.

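### Section 13 closes AE and SAE reporting 28 days after treatment, while Section 7.3.2 and Table 4 require AE reporting to study completion, and nothing says which rule governs

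*Protocol*

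**What the plan says.** Two sets of rules stand side by side in the protocol.

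The safety-reporting rules set a short window:
- Section 13.2.1, on AEs: "Adverse events are to be reported between from consent and 28 days after all the last study treatment". The sentence is garbled and still holds an unfilled placeholder where the study treatments should be listed, but the 28-day limit is clear.
- Section 13.1, on the definition of an SAE: "An SAE is any untoward medical occurrence that occurs between consent and 28 days after cessation of treatment interventions".
- Section 13.2.2, on SAE reporting to the coordinating centre: "from consent and within 28 days from the completion of treatment [SABR, RFA, MWA, TARE, TACE] is completed/discontinued".

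The assessment rules set a long one:
- Section 7.3.2 puts CTCAE v5.0 AE reporting at every visit, 3-monthly to 2 years and 6-monthly after that until the trial ends. It adds: "Assessment of toxicity is continuous and will include any event occurring between assessments".
- Table 4 ticks AE reporting at end of treatment, at 4 weeks, at months 3, 6, 9, 12, 15, 18, 21 and 24, and at 30+ months. Its key continues the last column every 6 months to study completion.

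Tables 2 and 8 define the safety endpoint as the cumulative incidence of AEs and give no time horizon. Section 1.5 gives toxicity a central place in the trial's intended conclusion: "Demonstration of a significant improvement in local control without increased toxicity" is what would support SABR as an initial treatment option.

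**The concern.** A site cannot obey both rules. A toxicity that starts in month 6 is due for reporting under Section 7.3.2 and Table 4, and is past the reporting limit under Section 13.2.1. No section gives one rule precedence.

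Three things are at stake. First, a stated secondary endpoint could be cut off at about 10 weeks after randomisation at sites that read Section 13 as binding. Secondly, if sites differ in their reading, cumulative incidence will mix short and long observation periods, and the missing part cannot be reliably recovered at analysis. Thirdly, the SAE definition itself contains the limit, so for serious events there is no competing rule to fall back on: a later event that meets every seriousness criterion is not an SAE. It then escapes the 24-hour report and the review of causality and expectedness in Section 13.2.2.

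The arms use different modalities, whose harms may appear at different times. The protocol itself says of one SABR effect: "Radiation-induced biliary strictures, and their associated distal segmental changes, can develop after SABR for more central tumours" (Section 1.6). A short window may therefore not treat the arms alike.

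**Working it through.** The plan states no figure of its own here, so the check is date arithmetic. Days are counted from randomisation and a month is taken as 30.4375 days.

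Inputs:
- Latest permitted end of primary treatment: day 42, in all arms (Section 6; Section 6.3.2 for SABR).
- Reporting limit: 28 days after the last study treatment (Sections 13.1, 13.2.1 and 13.2.2).
- Visit tolerance from month 3 on: 2 weeks either way (Section 7.3.2).
- Tolerance of the 4-week post-treatment visit: 1 week either way (Section 7.3.1).

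Step 1, closing day of the Section 13 window = day treatment ends + 28.
- Treatment ends on day 42: 42 + 28 = day 70.
- Treatment ends on day 1: 1 + 28 = day 29.

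Step 2, earliest permitted visit = months × 30.4375 − 14.
- Month 3: 91 − 14 = day 77.
- Month 6: 183 − 14 = day 169.
- Month 12: 365 − 14 = day 351.
- Month 24: 730 − 14 = day 716.

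The earliest 3-month visit falls 77 − 70 = 7 days after the latest possible closing day. For the window to reach that visit, treatment would have to end on day 77 − 28 = 49, a week beyond the limit. So all nine post-randomisation columns with an AE tick (3, 6, 9, 12, 15, 18, 21, 24 and 30+ months) lie outside the window.

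Step 3, visits that can lie inside it. These are the end-of-treatment visit and the 4-week visit only. The 4-week visit may take place 28 − 7 = 21 to 28 + 7 = 35 days after treatment, so it too can fall up to a week after closure. If it is held early, the look-back at month 3 would cover at most the last 28 − 21 = 7 days of the window.

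Step 4, share of 24 months outside the window = (24 × 30.4375 − closing day) / (24 × 30.4375), where 24 × 30.4375 = 730.5.
- Closing day 70: (730.5 − 70) / 730.5 = 0.904, about 90%.
- Closing day 29: (730.5 − 29) / 730.5 = 0.960, about 96%.

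**The case against.** The best defence is that Section 13 is unadapted template text and that sites will work from the schedule. Much supports this. The AE definition in Section 13.1 has no time limit; only the SAE definition does. Section 13.2.1 asks for the highest grade since the last visit and stops recording only for AEs unresolved at the last study visit, which suits long follow-up. Section 13.3 makes a new non-HCC cancer an AE or SAE with no limit, and Section 11.1 wants SAE-related procedures captured until withdrawal from the study. The placeholder points the same way. This stands in part: late AEs are lost only where Section 13 is followed, so loss from the endpoint is possible and not certain. It does not remove the contradiction, and it does not help with SAEs, where the limit is explicit in both the definition and the reporting rule.

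Three stronger readings are tempting, and the documents do not support them.
- A reader might infer that a late hospitalisation, for example for hepatic decompensation in month 4, would be invisible to the coordinating centre and the safety committee. Section 7.3.2 records hospitalisations, ascites, encephalopathy, Child-Pugh score and liver chemistry at each visit, and the committee reviews safety data every 6 months (Section 14.5.2). What is lost is SAE status and the expedited review that goes with it.
- A reader might infer that the bias must favour SABR. The 3-to-12-month changes in Section 1.6 are imaging changes, and no onset time is given for biliary strictures. Section 1.4 gives SABR toxicity rates without timing. No onset times are given for the comparators, and standard of care in Cohort 2 may include TARE, which the protocol also treats as radiation-based.
- A reader might infer that the window is systematically longer in one arm. It closes on a different day for each patient, but the 28-day and 42-day limits are the same in every arm, and either arm may finish first.

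**Conclusion.** The protocol contradicts itself on how long AEs are reported, and it restricts SAEs to a window that ends by day 70. Nine of the nine post-randomisation AE columns, and 90% to 96% of the 24-month follow-up, lie outside that window. Following Section 13 as written would truncate a stated secondary endpoint; following it at some sites only would make that endpoint non-comparable across sites. Serious events after 28 days miss 24-hour reporting and the causality and expectedness review under either reading.

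If treatments differ in when their harms occur, the comparison behind the toxicity conclusion in Section 1.5 may be biased. The documents do not allow the size or direction to be stated.

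The figures assume that treatment ends within the 42-day limit, that study treatment means the primary protocol therapy and not treatment after progression, and that visits keep to the stated tolerance. The contradiction depends on none of these. It needs correcting in the protocol, because an analysis plan cannot recover events that sites were told not to report.

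**What to change.** Amend Sections 13.1, 13.2.1 and 13.2.2 so that they agree with Section 7.3.2 and Table 4:
- Collect AEs in all arms over the same period from randomisation as the scheduled visits, and say so in one place. The exact period is for the sponsor to set.
- State how a serious event more than 28 days after treatment is reported when it may be treatment-related, including who reviews causality and expectedness. Remove the time limit from the SAE definition or add a separate rule for late events.
- Give the cumulative-incidence safety endpoint in Tables 2 and 8 a time horizon, for example 24 months to match the 2-year FFLP, PFS and OS endpoints.
- Fill in the list of study treatments in Section 13.2.1.

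The cost is a protocol amendment, a notice to sites and some additional SAE paperwork. The visits and the AE reporting at them are already in Table 4, so no new assessments are needed. Where sites have already applied the 28-day limit, late events should be sought from visit records before they become hard to recover.
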